## Abstract

**Background:**

Children living with HIV (CLHIV) and children who are exposed to HIV but uninfected (CHEU) are at increased risk of developing malnutrition. Severely malnourished children have high mortality rates, but mortality is higher in CLHIV/CHEU. This study aims to investigate whether empiric use of an antibiotic with greater antimicrobial sensitivity (ceftriaxone) than standard-of-care (ampicillin plus gentamicin) will reduce mortality among CLHIV/CHEU admitted with severe acute malnutrition.

**Methods:**

This is an open label randomized controlled trial involving 300 children; 76 CLHIV and 224 CHEU. The participants are being randomized to receive 1 week of ceftriaxone (*n* = 150) or standard-of-care (ampicillin/gentamicin) (*n* = 150), in addition to other routine care. The trial's primary outcome is in-hospital mortality. Secondary outcomes are: length of hospitalization; weight-for-height, weight-for-age and height-for-age z-scores; and pattern/antimicrobial sensitivity of pathogens. In addition, 280 severely malnourished children of unknown serostatus will be tested for HIV at admission to determine the prevalence and factors associated with HIV-infection. Furthermore, all the CLHIV on LPV/r will each provide sparse pharmacokinetic (PK) samples to evaluate the PK of LPV/r among malnourished children. In this PK sub-study, geometric means of steady-state LPV PK parameters [Area Under the Curve (AUC) _0−12*h*_, maximum concentration (C_max_) and concentration at 12 h after dose (C_12h_)] will be determined. They will then be put in pharmacokinetic-pharmacodynamic (PK-PD) models to determine optimal doses for the study population.

**Discussion:**

This study will ascertain whether antibiotics with higher sensitivity patterns to common organisms in Uganda and similar settings, will produce better treatment outcomes. The study will also provide insights into the current pattern of organisms isolated from blood cultures and their antimicrobial sensitivities, in this population. In addition, the study will ascertain whether there has been a significant change in the prevalence of HIV-infection among children presenting with severe malnutrition in the WHO recommended option B plus era, while determining the social/structural factors associated with HIV-infection. There will also be an opportunity to study PK parameters of antiretroviral drugs among severely malnourished children which is rarely done, and yet it is very important to understand the dosing requirements of this population.

**Trial Registration:**

ClinicalTrials.gov, identifier: NCT05051163.

## Introduction

Children living with HIV (CLHIV) are prone to developing malnutrition owing to medical and social factors including: higher daily calorie and micronutrient requirements than children who are unexposed to and uninfected with HIV (CHUU), a high frequency of infections including diarrhea which is often persistent/chronic, reduced intake because of a poor appetite and oral sores, late presentation to hospital, delayed initiation of antiretroviral therapy (ART) and food insecurity in households affected by HIV (1). CHEU have also been observed to be at risk of malnutrition; a prospective study among infants in Zimbabwe reported that they had lower mean weight-for length during follow up than CHUU (2). Because malnourished children are at risk of death, approaches that reduce mortality among CLHIV and CHEU who develop severe malnutrition, need to be evaluated.

Severely malnourished children have a high case fatality rate when admitted; studies in the East African Countries of Kenya, Tanzania and Uganda have reported mortality rates of 18–28% (3–5). HIV infection was associated with mortality in Uganda (4); similar to what had been observed in an earlier meta-analysis of data from Sub Saharan Africa (6). At the Mwanamugimu Nutrition Unit, Mulago Hospital, Uganda, studies conducted between 2001 and 2004 showed that ~40% of children admitted with severe acute malnutrition were HIV-infected (7–9). The overall mortality at the unit was 24% (4); but in a sub-analysis of those with bacteraemia, mortality was higher among the CLHIV than CHUU (43.5 vs. 20.5%) (8). CHEU were not identified in this study. More recent studies, in 2013 and 2017, at the unit have reported an HIV prevalence among the severely malnourished children of 24 and 12%, respectively. In these studies, a much higher mortality was observed among the CLHIV (33 and 47%, respectively) than in the CHUU (5 and 22%, respectively) (4, 10). The mortality rate among the CHEU in the 2017 study was 36% (4). Mortality therefore was more similar in CHEU and CLHIV than in CHUU. Preliminary audits at the unit indicate that 80–90% of the deaths are due to severe pneumonia and/or acute diarrhea. Late presentation and late initiation of ART play a role in increased mortality risks in CLHIV, (11, 12) but that cannot explain raised mortality risks in CHEU.

The WHO recommends that severely malnourished children receive empiric treatment with antibiotics for presumed bacteremia. This is because the typical signs of infection like fever may not be present in malnourished children given their impaired immunological response (13). The 2013 guidelines for management of severely malnourished children recommend amoxicillin for children admitted with severe acute malnutrition with no apparent signs of infection and no complications. Those with complications should receive ampicillin for 2 days followed by amoxicillin for 5 days, plus gentamicin for the 7 days of ampicillin/amoxicillin (i.e., combination treatment); if there is no improvement in 48 h, chloramphenicol is added for 7 days (13). This is the current practice in Uganda (14). However, these recommended drugs may no longer be effective in Uganda and elsewhere due to high rates of observed antimicrobial resistance (7, 8, 15, 16). On the other hand, studies have reported favorable susceptibility patterns to ceftriaxone (7, 8, 16, 17). It is therefore important to investigate, in these settings, whether antibiotics with higher sensitivity scores to common organisms, such as ceftriaxone, will produce better treatment outcomes. It is also necessary to ascertain whether there has been a change in the pattern of organisms isolated from blood cultures and their antimicrobial sensitivities.

Studies in Tororo, Uganda and South Africa have suggested that malnutrition may have an impact on the bioavailability of antiretroviral drugs including lopinavir/ritonavir, which is currently an alternative drug in first and second-line ART regimens in Uganda (18). Sub-optimally dosed antiretroviral drugs in HIV-infected severely malnourished children may therefore contribute to the poor outcomes we observe (19, 20).

This study aims to investigate whether empirical use of an antibiotic with greater antimicrobial sensitivity (ceftriaxone) than standard of care (ampicillin plus gentamicin) will reduce mortality among CLHIV and CHEU admitted with severe acute malnutrition at Mwanamugimu Nutrition Unit, Mulago Hospital. Secondary objectives include: to compare the length of hospitalization, weight-for-height, weight-for-age and height-for-age z-scores between ceftriaxone vs. standard of care (ampicillin and gentamicin) treatment arms. These anthropometric indices and length of hospitalization are hypothesized to be affected by infection related morbidity which may be influenced by the antibiotics received. Other secondary objectives include: to ascertain the frequency of different bloodstream bacterial pathogens and their antimicrobial sensitivities; to ascertain the prevalence of, and factors associated with, HIV-infection among children admitted with severe acute malnutrition at Mwanamugimu Nutrition Unit; and to evaluate the pharmacokinetic (PK) parameters of LPV/r among severely malnourished CLHIV.

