### Study Population

Three hundred children aged 1 month to 5 years (76 CLHIV and 224 CHEU) whose caretakers provide informed consent will be randomized to receive ceftriaxone (*n* = 150) or ampicillin plus gentamicin (*n* = 150). The 1 month to 5-year age group has been selected because it is the most affected by severe acute malnutrition and constitutes over 95% of admissions at Mwanamugimu Nutrition Unit. Also, the 1:3 ratio of CLHIV to CHEU in this sample is reflective of the current proportions of CLHIV and CHEU admitted at Mwanamugimu Nutrition Unit.

Three hundred randomized children provide >80% power to detect reductions in mortality from 28% (average across CLHIV and CHEU in preliminary audits at the unit) to 14% (50% relative reduction; absolute 14% improvement), allowing for 10% non-compliance/loss-to-follow-up (leaving hospital without official discharge) in each group. When half the participants have been enrolled (*n* = 150), the data safety monitoring board (DSMB) will review the preliminary data to determine if these estimates are appropriate. In addition, at least 280 severely malnourished children and their mothers will be tested for HIV at admission; any positive children will also be eligible to participate in the clinical trial. Two hundred eighty children provide 80% power to determine the prevalence of HIV-infection, using the prevalence of HIV-infection of 24% obtained in the probisam study in Mwanamugimu in 2013 (10), as a reference. The CLHIV in the clinical trial on LPV/r will take part in the pharmacokinetic sub-study providing 3 sparse PK samples each.

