### Participant Randomization

Randomization lists will be generated by the Trial statistician, using a computer, so that the study clinical team remain blinded about the allocation of the next child to be enrolled. The study coordinator will arrange for randomization codes to be printed onto cards placed in opaque sealed envelopes, a system that has worked well in other trials in acutely sick children. The envelopes will be stored on the ward and will be numbered consecutively and opened in numerical order by the study doctor.

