### Data Management and Statistical Analysis

A database will be designed to capture the patient data from the study tools. Data will be checked for completeness before entry into the database. The database will be backed up on a daily basis. The study tools for each patient will be put in separate folders and kept in lockable cabinets. The primary outcome will be in hospital mortality. Secondary outcomes will be: length of hospitalization (for those that are followed up till discharge); as well as weight-for-height, weight-for-age and height-for-age z-scores during follow up. The change in these anthropometric indices (z-scores) from admission to discharge will be determined, while controlling for the number of days of hospitalization. Another secondary outcome will be the distribution/antimicrobial sensitivity of pathogens.

Mortality (and other time-to-event data) will be compared between randomized groups using Kaplan Meier curves and Cox proportional hazards regression. WHO reference ranges will be employed to determine the anthropometric z-scores which will be analyzed using linear regression. Other categorical factors will be compared between randomized groups using chi-squared and exact tests, and continuous data using rank-sum tests. The statistical analyses will be performed in STATA version 15 (Stata Corporation, Houston, Texas).

Qualitative data from the in-depth interviews of the mothers will be analyzed using a content thematic approach, using *NVivo software*. We will enroll mothers and perform ongoing analysis until there is saturation of data.

For primary analysis in the PK sub study, sparse PK samples will be obtained from approximately 76 CLHIV. Using NONMEM version 7.3, PK-PD modeling and simulations will be performed to determine primary PK parameters, measures of plasma drug exposure and the dosing requirements.

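### The primary Cox comparison names no baseline covariate; prespecifying HIV status and admission values would be a small gain at no cost

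*Protocol article*

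**What the plan says.** All references are to the protocol article.

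- **Primary analysis** (Data Management and Statistical Analysis): "The primary outcome will be in hospital mortality". "Mortality (and other time-to-event data) will be compared between randomized groups using Kaplan Meier curves and Cox proportional hazards regression". No covariate or stratum is named, and the model is not said to be unadjusted.
- **Anthropometric outcomes** (same section): the change in each z-score from admission to discharge is assessed "while controlling for the number of days of hospitalization", by linear regression. This is the only adjustment variable named for any comparison between arms.
- **Randomisation** (Participant Randomization): "Randomization lists will be generated by the Trial statistician, using a computer". Stratification is neither stated nor excluded.
- **Earlier mortality at the unit** (Introduction): "a much higher mortality was observed among the CLHIV (33 and 47%, respectively) than in the CHUU". For the other enrolled group, "The mortality rate among the CHEU in the 2017 study was 36" per cent. The article concludes that CLHIV and CHEU resemble each other more than either resembles CHUU.
- **Sample size** (Study Population): 76 CLHIV and 224 CHEU, 150 per arm, with mortality falling from "28% (average across CLHIV and CHEU in preliminary audits at the unit") "to 14% (50% relative reduction; absolute 14% improvement"), more than 80% power, and 10% loss or non-compliance per group.
- **Order of events** (Study Procedures): HIV testing on admission, then anthropometry and physical examination at enrolment, then randomisation.

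**The concern.** The trial pools two groups whose mortality differed by 11 points in the 2017 study. Regression is already the chosen tool, and HIV status and admission measurements are in hand. Yet the one covariate named for a between-arm model, length of stay, arises after randomisation and is itself a secondary outcome, so it cannot do the work of a baseline covariate.

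There is little slack. Power is just above 80% for a 50% relative reduction that the Discussion itself calls unusual, and the Discussion rules out a larger trial on logistical grounds. Using baseline data is one of the few ways left to strengthen the comparison. The trial is also open label, so covariates chosen late would be easier to challenge than covariates named in advance.

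**Working it through.** **Inputs.** From the article: mortality 28% and 14%; 150 per arm, hence 150 × 0.9 = 135 evaluable per arm; 76 CLHIV and 224 CHEU; 2017 mortality 47% and 36%. Assumed because the article does not give them: two-sided alpha of 0.05, unstratified 1:1 allocation, and the prognostic strength of admission severity.

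**1. The plan's own power.** For two proportions with pooled variance, mean risk 0.21:

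z = [0.14 × √135 − 1.96 × √(2 × 0.21 × 0.79)] / √(0.28 × 0.72 + 0.14 × 0.86) = (1.627 − 1.129) / 0.567 = 0.877, so power is 81.0%.

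The requirement for 80% power is 132 per arm. 132 / 0.9 = 146.7, rounded up to 147 per arm, or 294 in total against 300 planned. The stated figure is reproduced.

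**2. How much of the outcome HIV status explains.** The CLHIV share is 76/300 = 0.253. Average 2017 mortality in this mix is 0.253 × 0.47 + 0.747 × 0.36 = 0.388. The share of variance explained is 0.253 × 0.747 × 0.11² / (0.388 × 0.612) = 1.0%.

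The design assumes a 28% average, so three versions consistent with 28% were examined:

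| CLHIV / CHEU mortality | Basis | Variance explained |
|---|---|---|
| 33.9% / 26.0% | 2017 rates scaled by 0.28/0.388 | 0.6% |
| 33% / 26.3% | 2013 CLHIV rate, CHEU solved for 28% | 0.4% |
| 47% / 21.6% | 2017 CLHIV rate, CHEU solved for 28% (extreme) | 6.1% |

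**3. Effect on power.** Cox models were simulated with 270 evaluable children and average risks held at 28% and 14% (3,000 trials per scenario, Monte Carlo error about 0.7 points).

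| Covariate | Scenario | Power, treatment only | Power, adjusted |
|---|---|---|---|
| HIV status | 33.9% / 26.0% | 81.4% | 81.2% |
| HIV status | 33% / 26.3% | 80.5% | 80.7% |
| HIV status | 47% / 21.6% | 81.0% | 83.3% |
| Severity (assumed) | log HR 0.4 per SD | 81.2% | 82.5% |
| Severity (assumed) | log HR 0.7 per SD | 81.9% | 86.2% |
| Severity (assumed) | log HR 1.0 per SD | 80.1% | 88.7% |

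HIV status therefore gives about 0 to 2 points, and severity about 1 to 9.

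In the strongest severity case the mean log hazard ratio moves from −0.79 to −0.90, while its standard deviation goes from 0.293 to 0.301. The gain comes from estimating a larger, conditional hazard ratio, not from a smaller standard error.

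**4. Chance imbalance in HIV status.** The number of CLHIV in one arm is hypergeometric, with SD = √(150 × 0.2533 × 0.7467 × 150/299) = 3.8 and a 95% range of 31 to 45. A 45/31 split shifts the raw risk difference by (45 − 31)/150 × 11 = 1.0 point. With the extreme gap of 47 − 21.6 = 25.4 points, the shift is 14/150 × 25.4 = 2.4 points. The target difference is 14 points.

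**5. Validity.** With no treatment effect and 300 children, simulated type I error was 4.3% to 4.6%, with or without adjustment.

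**6. z-scores.** With equal variances and correlation ρ between admission and discharge values, adjusting for the admission value gives a residual variance of σ²(1 − ρ²), against 2σ²(1 − ρ) for an unadjusted change. The ratio is (1 + ρ)/2, which never exceeds 1. The article gives no ρ, so no figure is attached.

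**The case against.** The strongest objection is that silence is not an error. A journal article may leave its covariate list and stratification factors to the full protocol or the SAP, neither of which is shown. A reader might infer that the analysis is unadjusted, or that a single unstratified list is used. The text says neither: it names no covariates, and it refers to lists in the plural. This stands, and it rules out saying that the trial ignores HIV status. What remains is that the article does name an adjustment variable for the z-scores, and that variable is not a baseline one.

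Three further points also stand.

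- The sharp mortality contrast in the Introduction is with CHUU, who are not enrolled. The relevant gap is 11 points from one study, between groups that the article itself calls more alike.
- A reader might infer that admission severity is known to predict death in these children. No passage shows it, so that part of the gain is assumption.
- A reader might infer that chance imbalance biases the result or undermines the power statement. It does neither: randomisation keeps the unadjusted test valid, and 81.0% is reproduced.

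It can also be objected that PCR for young children is done in another laboratory, and the article does not say that the result is back before randomisation. This affects when the status is known, not whether it is a baseline characteristic.

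**Conclusion.** The point holds as a low-severity improvement. As described, the mortality model names no baseline covariate and the z-score models name only a post-randomisation one, although suitable baseline values are already collected. Nothing in the article is shown to be biased or miscalculated.

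The size is modest. Adjustment for HIV status is worth about 0 to 2 points of power. Adjustment for severity is worth about 1 to 9 points, and that range reflects only the strengths assumed. A CLHIV imbalance at the edge of its 95% range moves the risk difference by about 1 point on the 2017 gap. These figures rest on two-sided alpha of 0.05, 135 evaluable children per arm, unstratified allocation, and earlier mortality rates carrying over to this trial.

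**What to change.** Prespecify the following, or confirm that the SAP already does so:

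- The Cox model for mortality adjusts for HIV status (CLHIV or CHEU, by final classification of the status at enrolment), age and admission weight-for-height z-score.
- Each z-score model adjusts for its own admission value and HIV status.
- The unadjusted result is reported alongside each adjusted one, and the text states which is primary.
- The adjusted hazard ratio is described as conditional on the covariates, so it need not equal the unadjusted one.

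At the design rates about 270 × 0.21 = 57 deaths are expected. The mortality model has four terms including treatment, or about 14 deaths per term, so it is not overloaded.

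A standardised risk difference, on the scale of the sample-size calculation, and an arm-by-HIV-status interaction are optional additions that the point does not depend on.

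The cost is analysis wording only: no new data, visits or participants.

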## Materials and Methods

### Study Design

The main study will be an open label randomized controlled trial among HIV-infected/HEU severely malnourished children admitted at Mwanamugimu Nutrition Unit. The children will be randomized to receive 1 week of ceftriaxone vs. standard-of-care (ampicillin plus gentamicin), both in addition to other routine care. The trial will be open-label because, it is difficult and potentially unethical to blind intravenous drug administration. Secondly, a cross-sectional evaluation will be done among severely malnourished children at admission; testing them for HIV to determine the prevalence of HIV-infection among severely malnourished children in the option-B-plus era. In addition, qualitative data will be collected from mothers of CLHIV to understand the sociocultural/system facilitators of HIV transmission. Thirdly, a PK sub study will be conducted within the clinical trial to evaluate the PK parameters of LPV/r among these severely malnourished children using sparse PK samples.

### Study Setting

Mwanamugimu Nutrition Unit at Mulago Hospital is a specialized center for management of malnutrition. It is the largest such center in Uganda and acts as a practicum site for universities in Uganda, including Makerere University. It consists of 3 in-patient (stabilization, transition and rehabilitation) wards, an outpatient therapeutic feeding center, a laboratory, a pharmacy and a kitchen. It is run by a team of 3 pediatricians, 2–6 postgraduate doctors at a time, 2–5 intern doctors, 1–2 intern nurses, 1 intern pharmacist, 25 nurses, 3 nursing assistants, 2 nutritionists, 4 nutrition assistants, and a laboratory technician. In 2021, 737 severely malnourished children were admitted to the unit^1^. It is a government owned and government run institution, so the services are designed to be provided at no cost to the patient/caregiver.

### Study Population

Three hundred children aged 1 month to 5 years (76 CLHIV and 224 CHEU) whose caretakers provide informed consent will be randomized to receive ceftriaxone (*n* = 150) or ampicillin plus gentamicin (*n* = 150). The 1 month to 5-year age group has been selected because it is the most affected by severe acute malnutrition and constitutes over 95% of admissions at Mwanamugimu Nutrition Unit. Also, the 1:3 ratio of CLHIV to CHEU in this sample is reflective of the current proportions of CLHIV and CHEU admitted at Mwanamugimu Nutrition Unit.

Three hundred randomized children provide >80% power to detect reductions in mortality from 28% (average across CLHIV and CHEU in preliminary audits at the unit) to 14% (50% relative reduction; absolute 14% improvement), allowing for 10% non-compliance/loss-to-follow-up (leaving hospital without official discharge) in each group. When half the participants have been enrolled (*n* = 150), the data safety monitoring board (DSMB) will review the preliminary data to determine if these estimates are appropriate. In addition, at least 280 severely malnourished children and their mothers will be tested for HIV at admission; any positive children will also be eligible to participate in the clinical trial. Two hundred eighty children provide 80% power to determine the prevalence of HIV-infection, using the prevalence of HIV-infection of 24% obtained in the probisam study in Mwanamugimu in 2013 (10), as a reference. The CLHIV in the clinical trial on LPV/r will take part in the pharmacokinetic sub-study providing 3 sparse PK samples each.

